The effectiveness of the intervention will be evaluated using a randomized controlled trial. Eligible children and their parents will be randomly assigned to the experimental group or a wait-list control group. Quantitative measures will be taken at baseline, at the end of intervention period (accelerometer measure will be taken during a period that included the day of the tenth intervention session, secondary outcomes will be taken the week immediately before the session) and post-intervention follow-up (one year after baseline), for all children and their parents who took part in the intervention. The primary outcome of the trial will be time children’s spent in leisure-time MVPA, measured objectively using accelerometers.

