### Objectives and hypotheses

The main objective of the current trial is to evaluate the effectiveness of a family-based physical activity intervention regarding changes in the objective measurement of the physical activity behaviors of parents and their children. We will also investigate the potential mediating effects of perceived parental autonomy support and controlling behaviors on children’s psychological need satisfaction or thwarting, and in turn their activity behaviors. Furthermore, we will examine how the intervention was perceived by the participants and whether it successfully initiated behavior changes through qualitative interviews. We hypothesize that relative to children and parents in the control group, participants in the experimental group will show significantly greater increases in MVPA from baseline to both post-intervention time points. We also hypothesize that children in the experimental group will report higher levels of perceived parental autonomy support, and lower parental controlling behaviors, when compared to their control group counterparts. Potential mediation effects of needs satisfaction and motivation on behavioral and health outcomes will be examined using structural equation modelling methods.

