### Procedures and randomization

Measures for primary and secondary outcomes will be taken at baseline, at the end of intervention period (accelerometer measure will be taken during a period that included the day of the tenth intervention session, secondary outcomes will be taken the week immediately before the session), and post-intervention follow-up (i.e., one year after the baseline measurement) to examine long-term intervention effects. After completing baseline measures, participants will draw a sealed envelope to determine whether they will be allocated to the experimental group or the wait-list control group. In each school, half of the recruited families will be allocated to the experimental group, and the other half will be allocated in the wait-list control group (i.e., 1:1 ratio). Participants allocated to the experimental group will receive ten bi-weekly intervention sessions over approximately 6 months immediately after baseline measures are taken. Participants allocated to the control group will be asked to attend measurement sessions, but they will only receive the intervention 12 months later (i.e., after the final follow-up time point). Each family will receive a HK$100 gift voucher for each completed assessment for the child and at least one parent. Intervention sessions will take place within school premises. All intervention sessions for a particular class will be led by the same activity leaders (two per session) throughout the intervention period. To encourage participation, each family will receive a transportation subsidy of HK$40 for the interactive workshops and activity sessions that they attend.

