The intervention also includes multiple components associated with specific behavior change strategies [40], and target specific theoretical constructs (see Table 1). The main intervention period will last for approximately 6 months, the length of intervention may vary among participating schools because of the differences of their academic calendars (exam periods, public or school holidays, and school activities would be avoided during the intervention to minimize disturbances to regular school activities). Participants will attend ten biweekly 90-min intervention sessions. Each session will consist of two parts, a 30-min interactive workshop followed by a 60-min activity session. An additional booster session will be provided approximately three months after the tenth intervention session. Both fathers and mothers will be invited to the intervention sessions, and at least one parent must be present during each intervention session.

**Table 1 Tab1:** List of intervention components and associated dosage, behavior change strategies, and hypothesized mediators

Intervention components	Dose	Description	Behavior Change techniques using Michie et al.’s [40] taxonomy	Hypothesized mediators
1. Interactive workshop	Ten 30-min biweekly sessions	Storytelling will be the critical teaching strategy for the workshops. There will be different stories and themes for each of the workshop; for instance, the key concepts of SDT and the ‘SAAFE’ teaching principle, the importance and benefits of the routinizing physical activity. A strong focus will be on ways to increase parent’s need support and reduce controlling behaviors, in which the differences between supportive and controlling behaviors will be illustrated with real-life examples.	- Goals and planning - Feedback and monitoring - Social support - Shaping knowledge - Natural consequences - Repetition and substitution - Identity	- Need support/ controlling behaviors - Competence - Autonomy - Relatedness - Autonomous motivation
2. Activity session	Ten 60-min biweekly sessions	Parents and children will attend activity sessions together. Sessions include rough and tumble play, and FMS training.	- Feedback and monitoring - Social support - Shaping knowledge - Comparison of behavior - Repetition and substitution	- Need support/ controlling behaviors - Competence - Autonomy - Relatedness - Autonomous motivation

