### Statistical methods

Data analyses will be conducted using linear mixed models using an intention-to-treat approach. Group differences concerning all primary and secondary outcomes will be examined. Specifically, a two-level (i.e., level 1 = time, level 2 = individual) model will be examined for each outcome, using the equation: Outcome = B_0_ + B_1_*Time + B_2_*Group + B_3_*Time*Group. The B_1_ coefficient will be parameterized as a variable with random slope and random intercept at all levels. Additional analyses will be conducted by adding the potential covariates and mediators to the models. An intervention effect will be deemed to be present if the B_3_ coefficient was statistically significant from zero.

Structural equation modelling will also be used to test the structural model of children’s perceived need support/control predicting need satisfaction/thwarting, and in turn physical activity behaviors and well-being. In the same model, we will examine the relationship between parents’ self-reported need supportive/controlling behaviors and children’s perception of the same constructs. Based on the work of Radel, Sarrazin, Legrain, and Wild [56], we will also examine the link between parents’ need satisfaction and their parenting styles in the model. To account for the relatively small sample size, a Bayesian approach will be used for structural equation modelling analyses (e.g., [53]).

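### Families are randomised, but the model has no family level: if mothers and fathers are pooled, standard errors for the secondary parent outcomes are too small

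*Protocol article*

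**What the plan says.** **Unit of allocation.** Procedures and randomization (Protocol article) splits families within each school: "half of the recruited families will be allocated to the experimental group", with the remaining half on the wait list. Two parents of one child therefore always share an arm.

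**Who takes part and is measured.** The Intervention section states: "Both fathers and mothers will be invited to the intervention sessions, and at least one parent must be present during each intervention session". The last paragraph before Objectives and hypotheses says that measures are taken "for all children and their parents who took part in the intervention". The gift voucher in Procedures and randomization is paid "for each completed assessment for the child and at least one parent". One parent is thus the minimum for an assessment, and two are possible.

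**Parent outcomes.** Primary and secondary outcomes of the trial lists, as secondary, parents' MVPA, FMS competency, BMI, provision of need support and psychological control, need satisfaction and thwarting, motivation, and well-being. Objectives and hypotheses also names parents in the lead hypothesis: "relative to children and parents in the control group, participants in the experimental group will show significantly greater increases in MVPA".

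**Model.** Statistical methods covers all primary and secondary outcomes with one two-level specification, "level 1 = time, level 2 = individual". It has fixed terms for time, group and their product, and random intercepts and slopes at those levels. An effect is declared when B3, the time-by-group coefficient, differs significantly from zero. The section gives no family level, no clustered variance, no rule choosing one parent per family, and no separate models for mothers and fathers.

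**The concern.** The analysis should respect the unit that was randomised. A mother and father from one family are one randomised unit, not two. They also share the sessions, the joint homework, the planning consultations and the scheduling help, so their changes could well move together. A random intercept and slope for each individual do not represent a change that is common to the couple. If both enter one model as separate individuals, the model counts more independent information on B3 than the randomisation supplies. Its standard error is then too small and its 5% test rejects too often.

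At stake are the claims about parents. These outcomes are secondary, but parents' activity is part of the stated main objective, and the same specification applies to all seven groups of parent outcomes.

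**Working it through.** **1. The plan's own figure.** Sample size calculation gives d = 0.5, alpha 0.05 and power 0.8. A two-sample t-test (two-sided, which is assumed because the text does not say) needs 64 per arm, N = 128, with power 0.801. Allowing for 30% accelerometer non-compliance and 10% drop-out: 128 / (0.70 × 0.90) = 203.2, rounded up to 204. Both figures reproduce. They concern children's MVPA and play no part in what follows.

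**2. Inputs that the documents do not give.** Both are assumptions, shown as ranges:
- f, the share of families in which both parents are measured and pooled in one model;
- r, the within-couple correlation of *change*. B3 tests change by group, so stable similarity between spouses largely cancels. A cross-sectional spouse correlation is not the relevant figure.

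**3. Design effect.** Let family i contribute m = 1 or 2 parents. Over F families, the sum of m is F(1 + f) and the sum of m(m − 1) is 2fF. The variance of a mean change, relative to independence, is therefore

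DE = 1 + [2f / (1 + f)] × r.

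The model's standard error is too small by 1 − 1/√DE, and the true two-sided type I error at nominal 5% is 2 × [1 − Φ(1.96/√DE)].

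Example with f = 0.5 and r = 0.3: DE = 1 + (1.0/1.5) × 0.3 = 1.20. The standard error is 1 − 1/√1.20 = 8.7% too small. 1.96/√1.20 = 1.789, which gives a type I error of 7.4%.

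| f | r | DE | SE too small by | Type I error |
|---|---|---|---|---|
| 0.5 | 0.1 | 1.067 | 3.2% | 5.8% |
| 0.5 | 0.2 | 1.133 | 6.1% | 6.6% |
| 0.5 | 0.3 | 1.200 | 8.7% | 7.4% |
| 1 | 0.1 | 1.100 | 4.7% | 6.2% |
| 1 | 0.2 | 1.200 | 8.7% | 7.4% |
| 1 | 0.3 | 1.300 | 12.3% | 8.6% |

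Outside this range: at f = 0.25 the error is 5.5% to 6.4% for r = 0.1-0.3. At r = 0.5 it is 9.0% for f = 0.5 and 11.0% for f = 1.

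**4. Simulation check.** Change scores were simulated with no true effect, 10,000 replicates per setting. With 204 families and f = 1, the individual-level test rejected in 6.2%, 7.4% and 8.9% of replicates at r = 0.1, 0.2 and 0.3. With f = 0.5 the figures were 5.7%, 6.8% and 7.1%. Results with 128 families were similar. A test on family means rejected in 4.6% to 5.35% of replicates across all settings.

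**5. Allowance for lost accelerometer data.** For parents' MVPA, f is cut by missing wear time. Assume that the children's rates apply to parents and act independently within couples, so retention is 0.70 × 0.90 = 0.63. Even if every family enrolled two parents, the share with two valid parents among families with any would be 0.63² / (1 − 0.37²) = 0.397/0.863 = 0.46. At f = 0.46, DE is 1.063 for r = 0.1 and 1.189 for r = 0.3, giving type I errors of 5.7% and 7.2%. The other parent outcomes do not depend on accelerometer wear.

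**The case against.** The strongest reply is that the text never says mothers and fathers are pooled. The section fixes the levels of the model, not who enters a parent model. One parent per family, or a separate model for each parent, would also be a model of time within individual and would produce no inflation. This stands, and it makes the point conditional. A reader might infer that spouses will certainly be analysed as independent and that parent effects will be over-declared. The documents do not establish that.

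Second, being invited to sessions is not the same as being measured. The voucher rule asks for only one parent, so f could be low. This also stands: no passage gives a number, and at f = 0.25 the inflation is small.

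Third, a reader might take the shared household as evidence of a large r. Stable likeness between spouses largely drops out of B3, so only joint change counts.

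Fourth, a reader might extend the point to children through siblings, or to the sample size. The article does not mention enrolling siblings, and the calculation of 128 and 204 concerns one child outcome.

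What does not stand is the reply that an analysis plan, which is not shown, may settle it. The article does not leave the levels open. It states them, for each outcome, without the unit it randomised. The additional analyses with covariates and mediators do not supply a family level either.

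**Conclusion.** The point holds in conditional form. If both parents of a family are pooled in one model, as the text allows, and their changes are positively correlated, the model as specified gives too small a standard error for B3 on the secondary parent outcomes. For r = 0.1-0.3, the true error of a nominal 5% test is about 6-7% when half the families contribute two parents and about 6-9% when all do. For parents' MVPA, missing accelerometer data probably keeps it toward the lower part of that range.

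The figures rest on assumed f and r. The effect is moderate because a family has at most two parents. The analysis of children's MVPA, the primary outcome, and the target of 204 are unaffected. It is still worth correcting, because the stated rule does not match the stated randomisation and the remedy is simple.

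**What to change.** Amend Statistical methods so that, for parent outcomes, it states one of the following:

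- keep the two-level model but use standard errors clustered on family;
- add a family level (time within parent within family) with a random intercept and a random time effect. A family intercept alone would not be enough, because B3 concerns change;
- fit mothers and fathers in separate models.

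The first and third are the simpler choices. With three time points and at most two parents per family, the full three-level model may be hard to fit on top of the individual random intercept and slope. Whichever is chosen, the section should also say which parents enter each model.

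The cost is slightly wider intervals for parent outcomes, or two models per outcome if mothers and fathers are separated. Recruitment, conduct and data collection do not change.

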### Sample size calculation

A power calculation was conducted to estimate the required sample size. Power calculation was based on the primary outcome of children’s MVPA, at the primary time point of 6-months. Calculations were conducted using G*Power 3.1.7. Based on the Healthy Dads, Healthy Kids study [29], intervention effect size was estimated at *d* = 0.5. With a Type I error probability of 0.05 and power of 0.8, the required sample size was calculated to be *N* = 128. To account for an estimated accelerometer non-compliance rate of 30% (i.e., cases with insufficient wear time) and a potential drop-out rate of 10% [14], a minimum of *N* = 204 children will be recruited.

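### The planned model frees a baseline group difference that randomization makes zero in expectation, so the test of B3 is valid but less precise than a common-baseline or baseline-adjusted analysis

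*Protocol article*

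**What the plan says.** Three parts of the protocol article bear on this point.

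- **Procedures and randomization** fixes the order of events: "After completing baseline measures, participants will draw a sealed envelope". Allocation is 1:1 within each school.
- **Statistical methods** sets a two-level mixed model for each outcome, "Outcome = B_0_ + B_1_*Time + B_2_*Group + B_3_*Time*Group", and makes the test of B3 the criterion for an intervention effect. Covariates enter only in additional analyses, and baseline MVPA is not named among them.
- **Sample size calculation** takes 6 months as the primary time point. On the effect it says "intervention effect size was estimated at *d* = 0.5". It continues: "With a Type I error probability of 0.05 and power of 0.8", "the required sample size was calculated to be *N* = 128". That is raised to 204 for an "estimated accelerometer non-compliance rate of 30% (i.e., cases with insufficient wear time") and "a potential drop-out rate of 10"%.

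The article does not state the correlation between waves, the SD that standardizes d, whether Time is linear or categorical, or whether the 30% wear loss also applies at baseline.

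**The concern.** Because allocation follows baseline, the two arms share one baseline population mean, and any observed baseline difference is chance. A model with a free B2 estimates that chance difference and subtracts it in B3. The noise in the baseline means is then carried into the treatment effect.

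Two things are at stake. The analysis gives up precision that the collected data already offer. The sample size also matches a plain two-group comparison of a single score, whereas the decision rests on a change from baseline. The variance of that change depends on a correlation that the calculation never mentions.

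**Working it through.** **1. The plan's own figures.** Inputs from Sample size calculation: d = 0.5, alpha 0.05 (taken as two-sided), power 0.8. A two-sample t-test needs 64 per arm, N = 128, with power 80.1%. Inflation: 128/(0.7 × 0.9) = 203.2, or 204 with equal arms. Both figures are correct for a single-score comparison.

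**2. Variance of the two analyses.** Take complete data at baseline and 6 months, equal SD sigma and correlation rho.

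- Free B2 (change score): variance per child 2(1 − rho) sigma².
- Common baseline or ANCOVA: (1 − rho²) sigma².
- Ratio: (1 − rho²)/[2(1 − rho)] = (1 + rho)/2, which is below 1 whenever rho is below 1.

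At rho 0.3, 0.5 and 0.7 the ratio is 0.65, 0.75 and 0.85, so adjustment saves 35%, 25% and 15% of the variance. This step needs no assumption about d or wear loss.

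**3. Power with 64 complete pairs per arm.** Assume d = 0.5 in SDs of MVPA. The standardized effect is then 0.5/√(2(1 − rho)) for the planned test and 0.5/√(1 − rho²) for the adjusted one. Rho is an assumption, shown as a range.

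| rho | planned B3 | common baseline or ANCOVA |
|---|---|---|
| 0.3 | 66.0% | 83.7% |
| 0.4 | 72.7% | 86.5% |
| 0.5 | 80.1% | 90.0% |
| 0.6 | 88.1% | 93.9% |
| 0.7 | 95.2% | 97.6% |

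The planned test breaks even with the stated 80% at rho = 0.5, where 2(1 − rho) = 1. If d = 0.5 is instead in SDs of the change score, 64 complete pairs per arm give the planned test 80.1% at any rho.

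**4. Power with incomplete data.** Assume 102 recruited per arm, 10% dropout after baseline, 30% invalid wear independently at each of the three waves, categorical Time, exchangeable correlation and d in SDs of MVPA. Generalized least squares information was summed over all missing-data patterns to give the SE of the 6-month contrast.

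| rho | planned | common baseline |
|---|---|---|
| 0.3 | 65% | 84% |
| 0.4 | 71% | 86% |
| 0.5 | 77% (SE 0.185) | 89% (SE 0.156) |
| 0.6 | 85% | 93% |
| 0.7 | 93% | 97% |

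The planned contrast crosses 80% at rho of about 0.54. If every baseline record is valid and the follow-up losses stay the same, the planned test has 79% at rho 0.4 and 85% at rho 0.5. The threshold therefore moves with the baseline wear assumption.

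**5. Coding of Time.** Steps 3 and 4 treat B3 as the 6-month contrast, which requires categorical Time. With linear Time over 0, 6 and 12 months, complete data and exchangeable correlation, B3 is a slope difference. It then equals the comparison of change from baseline to 12 months. The planned-test power in step 3 carries over (to within the normal approximation) only if the 0.5 effect persists to 12 months.

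**The case against.** The strongest reply is that nothing here is wrong. A group-by-time mixed model is standard and unbiased, and it controls the type I error. It also matches the hypothesis in Objectives and hypotheses, which speaks of larger gains from baseline. The validity part stands: this is a loss of efficiency, not a faulty test. The appeal to the hypothesis does not stand. When the baseline means are equal by design, the group difference at 6 months is the difference in expected gain, so the common-baseline model answers the same question more precisely.

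The second reply concerns power, and it stands. A reader might infer that the trial is underpowered at realistic correlations. The protocol does not support that. It gives no rho and no SD for d, and it does not say that the 30% loss recurs at baseline. Under some admissible readings the planned test meets or exceeds 80%.

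A reader might also multiply 204 × 0.7 × 0.7 × 0.9 and conclude that only about 90 children inform B3. That is the count for a complete-pairs analysis. The planned mixed model also uses children with one valid wave. For the same reason, keeping those children is not an advantage peculiar to the common-baseline model.

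**Conclusion.** The point holds as one of efficiency. The planned B3 is valid and unbiased, but it is less precise than a common-baseline or baseline-adjusted contrast at every rho below 1. With complete data at two waves and equal variances, the avoidable share of variance is (1 − rho)/2.

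The shortfall against 0.8 is conditional. With categorical Time and d in SDs of MVPA, it arises for rho below 0.5 with 64 complete pairs per arm. It arises for rho below about 0.54 with 102 recruited per arm, 10% dropout and independent 30% loss at every wave. It does not arise with 64 complete pairs per arm if d is in change-score SDs. In the scenarios tabulated, the common-baseline analysis stays above 80% throughout. The incomplete-data figures also rest on an exchangeable correlation, without the random slope that the protocol mentions.

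The change is worth making because it uses data already being collected and leaves the question unchanged.

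**What to change.** - Code Time as categorical. Omit the Group main effect at baseline, so that both arms share one baseline mean, and fit Group effects at 6 and 12 months. ANCOVA on the baseline value with the same visit structure is an acceptable alternative.
- Do both steps together. Dropping B2 while keeping linear Time would force the effect onto a straight line from zero. With a true effect of 0.5 at both follow-ups and rho 0.5, that model returns 0.545 at 12 months.
- Name the 6-month contrast as the primary test, in line with the sample size section.
- Apply the same form to every outcome measured at baseline.
- State the assumed rho, the SD behind d = 0.5, and whether the 30% wear loss is per wave. Then give the power of the chosen contrast.

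The cost is a revised model statement, including the coding of Time, and a few sentences in the sample size section. No further data, staff or participants are needed.

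### The decision test is a single Time-by-Group slope over 0, 6 and 12 months, which gives almost no weight to 6 months, the declared primary time point

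*Protocol article*

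**What the plan says.** Three statements in the article bear on which time point decides the trial.

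- **Sample size calculation.** Power is computed for children's MVPA "at the primary time point of 6-months", with d = 0.5. "With a Type I error probability of 0.05 and power of 0.8", this gives N = 128, inflated to 204 for invalid accelerometer wear and drop-out.
- **Objectives and hypotheses.** The experimental group is expected to show "significantly greater increases in MVPA from baseline to both post-intervention time points".
- **Statistical methods.** Each outcome is modelled with an intercept, one Time term (B1), one Group term (B2) and one product term (B3). "The B_1_ coefficient will be parameterized as a variable with random slope and random intercept at all levels". The decision rule is: "An intervention effect will be deemed to be present if the B_3_ coefficient was statistically significant from zero".

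The Abstract places the assessments at baseline, 6 months and 12 months. No section defines a separate 6-month contrast.

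**The concern.** A single B1 with a random slope and a single B3 describe a straight line per child and one difference in slope between the arms. Over three equally spaced waves, a straight-line slope is governed by the two ends. The middle wave, here the primary time point, hardly enters.

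The primary conclusion could therefore be wrong in either direction. The planned effect could be present at 6 months and fade, and the trial would be declared negative. Nothing could happen by 6 months and a difference emerge by 12, and it would be declared positive.

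An effect that peaks at the end of the programme is plausible under this design. The 6-month accelerometer window includes the day of the tenth session, which only the experimental arm attends. After that, the article schedules only one booster session, about three months later.

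**Working it through.** **Inputs from the article:** d = 0.5 at 6 months; alpha 0.05; power 0.80; 1:1 allocation; waves at 0, 6 and 12 months; 30% invalid wear; 10% drop-out.

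**Assumptions, not in the article:** between-wave correlation ρ = 0.5 (range 0.4 to 0.6); random-slope variance 0 unless stated; 12-month effect between 0 and 0.5; pattern of missing data as listed in step 5. The outcome SD is 1.

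**1. The stated sample size reproduces.** A two-sided two-sample t-test with d = 0.5 needs 64 per arm (power 0.801), so N = 128. Inflation: 128 / (0.7 × 0.9) = 203.2, hence 204. This figure is not at fault.

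**2. Slope weights.** The weight at time t is (t − 6) / Σ(t − 6)². The denominator is 36 + 0 + 36 = 72, so the weights are −6/72, 0 and +6/72, that is −1/12, 0 and +1/12. With complete data, the generalised least-squares estimate under a random intercept and slope has the same weights. Hence 12 × B3 is exactly the group difference in change from baseline to 12 months.

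**3. Standard error.** With n per arm, Var(12 × B3) = (2/n) × 2(1 − ρ). For n = 64 and ρ = 0.5 this is (2/64) × 1 = 0.03125, so SE = 0.177.

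**4. Power with complete data** (normal approximation, power ≈ Φ(effect/SE − 1.96) plus the opposite tail):

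| Effect at 6 / 12 months | Effect/SE at ρ = 0.5 | Power, ρ = 0.5 | Power, ρ = 0.4 to 0.6 |
|---|---|---|---|
| 0.5 / 0.5 | 2.83 | 81% | 73–89% |
| 0.5 / 0.375 | 2.12 | 56% | 49–66% |
| 0.5 / 0.25 | 1.41 | 29% | 25–35% |
| 0.5 / 0.125 | 0.71 | 11% | 10–12% |
| 0.5 / 0 | 0 | 5% | 5% |
| 0 / 0.5 | 2.83 | 81% | 73–89% |

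A random-slope variance of 0.001 per month² adds 144 × 0.001 = 0.144 to 2(1 − ρ). At ρ = 0.4 this lowers the sustained-effect power from 73% to 68%.

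**5. Power with losses.** There are 204/2 = 102 per arm and ρ = 0.5. Combined loss at a later wave is 1 − 0.7 × 0.9 = 37%. Weights are for 12 × B3, and the 6-month effect is 0.5.

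| Missing at 0 / 6 / 12 months | Weights | Power for 12-month effect 0.5 / 0.375 / 0.25 / 0.125 / 0 |
|---|---|---|
| 30 / 37 / 37% | −1.02, 0.04, 0.98 | 79 / 56 / 30 / 12 / 5% |
| 0 / 37 / 37% | −1.08, 0.16, 0.92 | 91 / 73 / 47 / 22 / 8% |
| 0 / 30 / 50% | −1.14, 0.28, 0.86 | 90 / 74 / 52 / 29 / 12% |

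**6. Categorical reading.** With Time as a three-level factor there are two interaction coefficients, so the rule's single B3 does not identify one. A random intercept plus random effects on both visit indicators has 6 covariance parameters. Adding a residual variance makes 7, but three waves supply only 6 variances and covariances.

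**7. A 6-month contrast instead.** With 64 complete per arm and d = 0.5 at 6 months, power at ρ = 0.4 / 0.5 / 0.6 is 73 / 81 / 89% for the change from baseline and 87 / 90 / 94% for the baseline-adjusted difference. Neither depends on the 12-month effect.

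**The case against.** **The coding of Time is not stated.** The word linear describes only the model class, and a Time-by-Group product is common shorthand for a factor interaction. The hypothesis about both later time points would fit two visit contrasts. This stands as a caution: the power figures in steps 4 and 5 hold only for numeric Time. But one B1, one B3 and a random slope point to numeric Time, and the factor reading leaves the decision rule without a defined coefficient. Neither reading ties the rule to 6 months. Nor is this a detail left to the analysis plan, because the article itself prints the equation and the rule.

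**Missing data give 6 months some weight.** This stands in part. If baseline is nearly complete, power when the effect halves rises from about 30% to 47–52%, so partial fade is less damaging than the complete-data table suggests. After a complete fade it is still only 8–12%.

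**A sustained effect keeps the planned power.** True, at 73–89% with complete data over the assumed correlations. But the sample size calculation assumes nothing about 12 months, so the power of the primary test should not depend on what happens there.

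**A random slope is not always unidentifiable with categorical visits.** Also true. Factor fixed effects with one random linear slope use four covariance parameters and can be fitted. Dropping the random slope is therefore a recommended simplification and is not strictly forced.

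**Conclusion.** The concern holds. The decision rule is not aimed at the time point for which the trial is powered. On the natural numeric reading, B3 tests the 12-month change. The 6-month weight is exactly zero with complete, equally spaced data, and 0.04 to 0.28 (against roughly 1 at the other waves) in the loss patterns examined. With d = 0.5 at 6 months, the power of B3 runs from about 81% for a sustained effect to 5% for one that vanishes, at an assumed correlation of 0.5 with complete data. With losses, the vanishing-effect figure is 5 to 12%. An effect confined to 12 months is detected as readily as a sustained one when data are complete. The correlation, the 12-month effect and the missing-data pattern are all assumptions. Varying them changes the size of the loss but not the conclusion. This must be fixed, because it decides whether the trial is called positive.

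**What to change.** In Statistical methods:

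1. Replace the single Time term with a visit factor (baseline, 6 months, 12 months) and its interaction with Group.
2. Name the Group by 6-month contrast for children's MVPA as the primary test and the sole basis for declaring an intervention effect.
3. Report the Group by 12-month contrast as the key secondary estimate, of maintenance, and align the hypothesis about both later time points with that order.
4. Use an unstructured within-child covariance and delete the sentence on the random slope and intercept at all levels.

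Items 1 and 2 cure the defect. Items 3 and 4 make the model coherent with them.

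The cost is wording only, with no change to sample size, visits or data collection. The model gains two fixed effects (one more for visit, one more for the interaction) and two covariance parameters (six, against four for a random intercept and slope with their covariance and a residual).
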